## Abstract

**Background:**

Chronic low back pain (LBP) is a major public and occupational health problem, which is associated with very high costs. Although medical costs for chronic LBP are high, most costs are related to productivity losses due to sick leave. In general, the prognosis for return to work (RTW) is good but a minority of patients will be absent long-term from work. Research shows that work related problems are associated with an increase in seeking medical care and sick leave. Usual medical care of patients is however, not specifically aimed at RTW.

The objective is to present the design of a randomized controlled trial, i.e. the BRIDGE-study, evaluating the effectiveness in improving RTW and cost-effectiveness of a multidisciplinary outpatient care program situated in both primary and outpatient care setting compared with usual clinical medical care for patients with chronic LBP.

**Methods/Design:**

The design is a randomized controlled trial with an economic evaluation alongside. The study population consists of patients with chronic LBP who are completely or partially sick listed and visit an outpatient clinic of one of the participating hospitals in Amsterdam (the Netherlands). Two interventions will be compared. 1. a multidisciplinary outpatient care program consisting of a workplace intervention based on participatory ergonomics, and a graded activity program using cognitive behavioural principles. 2. usual care provided by the medical specialist, the occupational physician, the patient's general practitioner and allied health professionals. The primary outcome measure is sick leave duration until full RTW. Sick leave duration is measured monthly by self-report during one year. Data on sick leave during one-year follow-up are also requested form the employers. Secondary outcome measures are pain intensity, functional status, pain coping, patient satisfaction and quality of life. Outcome measures are assessed before randomization and 3, 6, and 12 months later. All statistical analysis will be performed according to the intension-to-treat principle.

**Discussion:**

Usual care of primary and outpatient health services isn't directly aimed at RTW, therefor it is desirable to look for care which is aimed at RTW. Research shows that several occupational interventions in primary care are aimed at RTW. They have shown a significant reduction of sick leave for employee with LBP. If a comparable reduction of sick leave duration of patients with chronic LBP of who attend an outpatient clinic can be achieved, such reductions will be obviously substantial for the Netherlands and will have a considerable impact.

**Trial registration:**

ISRCTN28478651

## Background

### Primary care in the Netherlands

In the Netherlands primary care for patients with low back pain (LBP) is given by general practitioners, occupational physicians, and allied health professionals e.g. physical therapists or occupational therapists. Usually a patient first visit a general practitioner. The general practitioner may treat the patient himself or refer the patient to a medical specialist in outpatient care and/or to an allied health professional in primary care. Since January 2006, patients do also have direct access to allied health professionals.

General practitioners and physical therapists have their own national clinical guidelines for LBP [1,2]. Medical specialists do not have clinical guidelines for LBP, although a multidisciplinary guideline has been developed and published in 2004 [3]. Usual care is assumed to be consistent with guideline recommendations.

Each Dutch company is obliged to have company insurance for sick leave and to offer their employees access to occupational health care. Occupational physicians provide social medical guidance for sick listed employees with the aim to return to work (RTW) as quickly as possible. Self-employed people, however, don't have access to occupational health care. They need to have a private insurance for incapacity for work, which is expensive. If they have insurance a physician working for an insurance company will guide the self-employed individual back to work. Occupational physicians also have their own national clinical guidelines [4].

### Low back pain

LBP is a major public and occupational health problem and associated with very high costs. The total annual cost of low back pain to Dutch society, is estimated to be € 4.6 billion per year. The economic burden of LBP is primarily related to indirect costs (93%) of productivity losses due to sick leave and long-term disability. The direct healthcare costs are much lower (7%) [5]. In general, the prognosis for RTW is good [6]. However, approximately 10% to 25% of patients will have long-term absenteeism from work and will be at risk of social and financial deprivation. These patients account for 75% of the indirect costs of LBP [7].

Research shows that work-related problems are associated with an increase in seeking medical care and sick leave [8]. Usual care of medical specialists, general practitioners and allied health professionals of patients sick listed due to LBP is not directly aimed at RTW and co-operation with occupational physicians is usually poor [9]. Besides the content of the usual care, also the limited information exchange between the treating and occupational physicians is often an obstacle for RTW [10,11]. Despite these findings, several studies indicate that medical specialists, general practitioners and occupational physicians are willing to improve cooperation and communication [12,13].

Because usual care of primary and outpatient health services isn't directly aimed at RTW, it is desirable to look for care which is aimed at RTW. Research shows that several occupational interventions in primary care are aimed at RTW. They have shown a significant reduction of sick leave for employee with LBP [14,15].

### Objectives

In this article, we describe the design of a randomized controlled trial (RCT) comparing multidisciplinary outpatient care with usual clinical medical care for patients with chronic LBP visiting an outpatient clinic. The multidisciplinary outpatient care program consists of two interventions: a workplace intervention and a graded activity intervention. This program will be compared to usual clinical medical care. The first question of this study is 'Is the multidisciplinary outpatient care situated in both primary and outpatient care setting for patients with chronic LBP effective for RTW and cost-effective compare to the usual clinical medical care?'. The second question is 'How is the program for multidisciplinary outpatient care and its implementation (i.e. the applicability, compliance to, perceived effectiveness, barriers) evaluated by patients with LBP, their employer and their health care professionals?'

## Methods/Design

### Study design

#### Organization of the study

The design of the study is an randomized controlled trial (RCT) with a full economic evaluation alongside. The conduct of the study is guided by a committee of representatives of all professional groups monitoring the implementation of the interventions in the study. The most important task of this committee was the critical appraisal of the study protocol on the feasibility of the interventions during the study.

The Medical Ethics Committees of the participating hospitals (the VU University Medical Centre, the Slotervaart hospital, the Amstelland hospital, the Onze Lieve Vrouwe Gasthuis, all based in Amsterdam, and the Spaarne hospital in Hoofddorp) approved the study. All participants will sign an informed consent and will be insured according to Dutch Law in case of any damage caused by participation in the study. Figure 1 shows a brief outline of the design of the RCT.

**Figure 1 F1:**
[figure not shown]
**Design of the RCT**. MS, medical specialist; GP, general practitioner; OP, occupational physician.

#### Participants

The population consists of LBP patients (18–65 years) who visit an outpatient clinic (mainly orthopaedics and neurology, but also rheumatology and neurosurgery) of one of the participating hospitals. The population has to 1. have LBP lasting more than 12 weeks, 2. have paid work (i.e. paid-employment or self-employed) for at least 8 hours a week and 3. be on (partially) sick leave. Patients will be excluded from the study in case of 1) being sick listed more than two years; 2) working temporarily for an employment agency without detachment; 3) having specific low back pain, due to infection, tumor, osteoporosis, rheumatoid arthritis, fracture or inflammatory process; 4) having had a lumbar spine surgery in the last 6 weeks or having to undergo surgery or invasive examinations in the near future (within 3 months); 5) having serious psychiatric disorders; 6) having cardiovascular or medical contraindications for physical activity according to the Physical Activities Readiness Questionnaire (PAR-Q) [16]; 7) being pregnant or having given birth in the last 3 months; 8) dealing with a lawsuit to their employer; 9) not having the ability to complete questionnaires written in the Dutch language.

In order to recruit a sufficient number of eligible patients, in each hospital a competent hospital employee will identify the source population weekly from the computerized patient record system. Within one week after the visit, the patients will receive three documents by mail: 1. a letter from their medical specialist in which they are informed about the study and asked if they are willing to participate, 2. a brochure with details of the study and 3. a short screening questionnaire. A return envelope is enclosed for returning the screening questionnaire to the researcher. On this questionnaire they can indicate if they are willing to participate in the study.

All patients who return the questionnaire, meet the criteria and indicate that they are willing to participate will be contacted by telephone. The researcher or a research assistant will provide additional information about the implications of participation and will check the eligibility of the patient. If a patient meets the selection criteria and is willing to participate, they will be asked to sign the informed consent.

#### Randomization

An independent statistic performs randomization, using a computer-generated random-sequence table. The randomization will be performed on patient level. The patients are stratified on 2 important prognostic factors before randomization to prevent an unequal distribution. The first prognostic factor is the duration of sick leave (less than or longer than 3 months). The second prognostic factor is job characteristics ((mainly) physical or mental work demands) [17]. This results in a total of 4 strata. For every stratum, block randomization of 4 allocations will be used to avoid unequal treatment group sizes.

The researcher will prepare for each stratum opaque, sequentially numbered, and sealed coded envelopes, with either a note for the multidisciplinary outpatient care group or a note for the UC group. If a patient meets all criteria he/she will be allocated to one of the four strata. The researcher hands over to the patient the first two envelopes (left over) of that stratum where the patient is asked to pick one of the envelopes, open the envelope and sign the note. After randomization, the researcher/assistant registers information in the database about the patient's employer, occupational physician, general practitioner, and medical specialist. Patients in the multidisciplinary outpatient care group choose one of the 10 physiotherapy practices, in which they will perform the graded activity program. After randomization, the researcher/assistant will make, for patients in the multidisciplinary outpatient care group, an appointment for a visit with the care manager of the multidisciplinary outpatient care program. This appointment will take place within one week after randomization.

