### Blinding

Patients, therapists and researchers cannot be blinded for the allocated treatment. Treatment allocation takes place after informed consent and completion of the baseline questionnaire. Most outcome measures are self-reported and consequently cannot be blinded. However, since all questionnaires are sent to the patient by mail, researcher and care providers are not likely to influence the way patients complete the questionnaires. In addition, the reliability regarding the self-reported data on RTW is checked by sick leave data derived from databases of occupational health services. The therapists of the multidisciplinary team (care manager, occupational therapist, physical therapist) are not involved in assessing any of the outcomes.

After randomization all patients receive their own code. A run-up number and the first two letters of the visited hospital compose this code. The research assistant will put all data in the computer by code. Therefore, the analysis of the data by the researcher will be blind.

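### Allocation is not securely concealed from the researcher, who fills and hands out the envelopes and may also screen patients

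*Protocol article*

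**What the plan says.** All references are to the protocol article, Methods/Design.

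- **Sequence generation (Randomization).** "An independent statistic performs randomization, using a computer-generated random-sequence table"; I read this as an independent statistician.
- **Strata and blocks (Randomization).** Sick-leave duration and type of work demands are crossed: "This results in a total of 4 strata". Then: "For every stratum, block randomization of 4 allocations will be used to avoid unequal treatment group sizes".
- **Envelopes (Randomization).** "The researcher will prepare for each stratum opaque, sequentially numbered, and sealed coded envelopes", each holding a note for one of the two groups.
- **Dispensing (Randomization).** "The researcher hands over to the patient the first two envelopes (left over) of that stratum". The patient picks one, opens it and signs the note.
- **Screening (Participants).** The researcher or a research assistant telephones candidates, explains what taking part involves and "will check the eligibility of the patient". Consent is signed after that.
- **Blinding.** "Patients, therapists and researchers cannot be blinded for the allocated treatment". Allocation follows consent and the baseline questionnaire.

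The article nowhere says that someone outside recruitment fills or holds the envelopes.

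**The concern.** Independent generation protects a trial only if the sequence stays away from those who recruit. Here it passes to the researcher, because whoever puts the notes into numbered envelopes has to know which note goes where. The same role may then describe the trial to a candidate, judge eligibility, assign the stratum and hand over the envelopes. Past allocations are visible because the trial is open, and a fixed block of 4 in each stratum lets that history be used to predict the next one.

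If the person who screens has an idea of the next arm, patients with better or worse prospects of returning to work can be steered, even unintentionally. The route is the telephone call, or a judgement such as whether a job counts as mainly physical or mainly mental, which decides the envelope stack. The primary outcome is analysed from self-report in an unblinded trial, so concealment is one of the main safeguards left. The planned adjustment for baseline differences reaches measured factors only, not motivation or an employer's goodwill.

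**Working it through.** The article gives no figure for predictability, so there is none to reproduce. The sample size (115 complete, 130 included) is not affected.

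**Inputs.** From the article: 130 patients, 4 strata, blocks of 4, two envelopes offered and one picked. Assumed: equal strata (130/4 = 32.5, so about 32 each), a random pick, and the unpicked envelope staying in the next pair.

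**1. Benchmark: blocks of 4 opened one at a time, history only.** Chance of a right best guess by position in the block:
- first: 1/2
- second: 2/3
- third: 1/3 × 1 + 2/3 × 1/2 = 2/3
- fourth: 1

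Mean = (0.500 + 0.667 + 0.667 + 1)/4 = 0.708. Certain allocations: (0 + 0 + 1/3 + 1)/4 = 0.333.

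**2. Two-envelope rule, contents known.** The arm is certain only when both envelopes hold the same arm.
- Two envelopes from one block match with probability 1/3; two from different blocks match with probability 1/2. If f is the share of pairs lying within one block, P(match) = 1/2 − f/6.
- Under random picks the held-over envelope lies 1, 2, 3, … places behind the newest with probability 1/2, 1/4, 1/8, …. When the newest is 1st, 2nd, 3rd or 4th in its block, the chance that the pair shares a block is 0, 1/2, 3/4 or 7/8. The sum is 2.125 per block.
- For 32 patients the newest envelope runs from number 2 to number 33. The first block contributes 3 (all its pairs lie inside it), the next seven contribute 7 × 2.125 = 14.875, and number 33 contributes 0. So f = 17.875/32 = 0.559.
- P(match) = 0.500 − 0.559/6 = 0.407. Over 130 patients that is 0.407 × 130 ≈ 53.
- Right guesses: 0.407 + 0.593 × 0.5 = 0.703.

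**3. Two-envelope rule, history only.** This was simulated, with the probabilities updated after each allocation (4,000 simulated strata of 32): 9.6% of allocations certain, best guess right 68.0% of the time, matching pairs 40.5%, which agrees with step 2. With 16 per stratum the figures are 9.3%, 67.5% and 39.9%, so stratum size matters little.

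| Situation | Certain | Best guess right |
|---|---|---|
| Full concealment | 0% | 50% |
| One at a time, history only | 33% | 71% |
| Two-envelope, history only | about 10% | about 68% |
| Two-envelope, contents known | about 41% | about 70% |

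**The case against.** The plan has real safeguards. The envelopes are opaque, sealed, numbered and coded, the sequence comes from an independent source, and allocation already follows consent and the baseline questionnaire. A hospital employee identifies the source population, screening starts with a mailed form, and most criteria are factual. An assistant may do the eligibility check, so the overlap of roles is permitted rather than established. Self-reported return to work is checked against occupational health records. All of this stands and narrows the room for steering. It does not close the gap: sealing shields the patient but not the person who filled the envelope, and the telephone call and eligibility check come before consent.

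Three stronger readings are tempting, and the article does not support them.

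- A reader might infer that whoever holds the list can foresee every allocation. The patient's pick prevents that: when the two envelopes differ, the outcome is a coin toss.
- A reader might infer that offering two envelopes is itself what breaks concealment. It lowers certainty from history from 33% to about 10%. Its drawback is that allocations leave the generated order, so the numbering is a weaker check.
- A reader might infer that no audit trail is left. Each patient signs the note in a coded, numbered envelope, so a record exists; only the check on order is weakened.

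**Conclusion.** The point holds in this form: allocation is not securely concealed from the researcher. It would be too much to say that allocation is unconcealed, since patients are shielded, or that selection bias has occurred. Bias is possible, not shown.

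The size rests on the assumptions above and on a recruiter who either knows the envelope contents or tracks each stratum's history. That the researcher sees the sequence is an inference from filling the envelopes; the article does not say how the table is passed on. The main weakness is knowledge of the contents, which makes about four allocations in ten certain against about one in ten from history. The fixed block size is secondary. The matter should be settled before recruitment, because selection on unmeasured factors cannot be removed in the analysis.

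**What to change.** 1. The independent statistician already in the plan keeps the list and prepares and seals the envelopes, or releases each allocation by telephone. Nobody who recruits or screens sees the sequence.
2. Eligibility and stratum are logged irrevocably before the allocation is revealed. The existing rule that consent and the baseline questionnaire come first is kept.
3. Once steps 1 and 2 are in place, open only the next-numbered envelope and use randomly varying block sizes that are not disclosed to the researcher.

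The two-envelope pick should not be dropped on its own. With the researcher still filling the envelopes, opening them in order would raise certainty from about 41% to 100% for someone who knows the contents, and from about 10% to 33% from history.

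The cost is a change of protocol wording, a few hours of the statistician's time, and slightly larger possible imbalance within strata from varying blocks. No extra patients or visits are needed.

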#### Interventions

##### 1. Multidisciplinary outpatient care program (MOC)

Multidisciplinary outpatient care is a case management program consisting of a workplace intervention protocol and a graded activity (GA) program. Two clinical occupational physicians were trained as care managers. The content of the interventions and the role of each member of the multidisciplinary team are described in detail below. The flow of the multidisciplinary outpatient care program is shown in Figure 2.

**Figure 2 F2:**
[figure not shown]
**Time schedule of the multidisciplinary outpatient care protocol**. GA, graded activity; GP, general practitioner; OT, occupational therapist; MS, medical specialist; OP, occupational physician; WI, workplace intervention; PT, physicial therapist; RTW, return to work.

##### MOC 1: Case management protocol

The multidisciplinary team providing the multidisciplinary outpatient care consists of the care manager, the occupational therapist, the physical therapist and the patients own medical specialist, general practitioner and occupational physician. The care manager has an intermediate role between primary and outpatient care. He is responsible for the planning and the coordination of care and for communication with the other care providers involved in the team.

The patient will visit the care manager within 1 week after randomization. The care manager starts with history taking and physical examination. History taking aims to identify functional limitations at work and factors that could be of influence for RTW, such as heavy work, organizational problems or inadequate treatment [4]. If the care manager has doubts about the clinical diagnosis or functional limitations of the patient, he contacts the patient's medical specialist, occupational physician or general physician. By the end of the first consultation, the care manager proposes a treatment plan, gives an estimate of the sick leave duration until full RTW and gives the patient a file for collecting all documents of the multidisciplinary team. If the patient agrees with the plan, the care manager will contact the patient's occupational physician in order to advise the plan for RTW. The final advise to the patient and his/her employer with respect to RTW will remain the responsibility of the patient's occupational physician. When the patient's occupational physician agrees with the plan, the care manager sends the communication form to the medical specialist, general practitioner, physical therapist and occupational therapist. All communication will be performed according to the GP-OP-coordination guideline from the Dutch general practitioner and occupational physician medical organizations [4,11]. The communication form contains information about the history taking and physical examination, personal information of the patient and a prognosis for the sick leave duration until full RTW.

To streamline the process, the care manager has access to an administrative database, which contains information about the health care professionals involved, the employer of patients and generates the tasks of the care manager per patient on a daily basis. One of the tasks is to organize a conference call every three weeks. A conference call will take place between the care manager, occupational therapist en physical therapist and the patient's medical specialist, general practitioner and occupational physician if relevant. After 6 and 12 weeks, the patient will visit the care manager again to evaluate progress and if necessary adjust the date of RTW.

